**Institutional Review Board**

No subject is to be enrolled on this protocol until the Center’s Institution Review Board has approved it.

# Monitoring

Monitoring plan development for this project is commensurate with the risks proposed by the project.

Monitoring will be ongoing by the principal investigator (PI-[name]), and the Institutional Review Boards (IRB) of Advarra. Overall, the plan for monitoring includes: 1) Monitoring the progress of the study; 2) Assuring compliance with the requirements for reporting adverse events that may occur during the study; and 3) assuring data accuracy and protocol compliance. For all study protocols, the PI is responsible for the reporting of adverse events to the IRB.

[name] will oversee the implementation of the study and daily monitoring. This will include weekly meetings to discuss any issues related to the progression of the project and factors that may affect the outcome, including a review of data quality and security, recruitment, and retention. Adverse events will also be discussed. A brief report will be created and submitted annually for the study record and submitted to the Advarra IRB. For any problems that may arise, [name] will consult with the co-investigators to discuss how to best proceed.

# Informed Consent

The investigators and the research staff are responsible for obtaining consent by the participants.

Caregivers and patients will be scheduled for their consenting session to occur in clinic, to coincide with a patient visit. Study staff will consent caregivers and patients separately. Caregiver consent will occur first, and if the caregiver consents, the patient will be invited to complete the informed consent process. Study staff will provide a detailed description of the study, answer questions, obtain informed consent, and finalize eligibility. Participants will be given as much time as needed to ask questions during the consenting process, prior to agreeing to participate in the study. From there, if the patient declines to participate, the caregiver may still participate. We believe this is the ethical approach (vs dropping the caregiver), as the caregiver already made the decision to participate, was informed about the intervention, and scheduled for treatment visits. Once consented, if either member of the dyad drops, the other will be allowed to remain in the study.

# STATISTICAL CONSIDERATIONS

### Data Management and Statistical Considerations

Descriptive statistics will be used to summarize and evaluate the distributions of all study variables. Transformations will be applied, as needed, prior to hypothesis testing. Missing data analyses will assess 1) prospective predictors of missingness that may influence interpretation and generalizability of results from hypothesis testing and 2) whether or not multiple imputation for managing missing data would be beneficial. Paired comparisons will be used to identify group differences, despite randomization, in demographics, clinical, and psycho-social variables that will then be included as covariates when testing hypotheses. Primary analyses for Aims 1 and 2 will use generalized estimating equations (GEE) with an identity link function, linear regression, and compound symmetry for the working correlation matrix. Advantages to using GEE, which fit population-averaged models, are to 1) assess changes in the outcome variable over time, 2) aggregate measures of the outcome variable across time to capture condition differences that may appear at different times for different participants, 3) assess primary hypotheses with targeted comparisons that incorporate data from all participants across multiple assessments, and 4) help effectively manage missing data by study completers under the missing at random assumption (MAR). The Holm method148 will be applied to control for experiment-wise error in the primary analyses, with alpha set at .025 for tests of FOCUS vs UC and set at .05 for FOCUS vs HL. Primary analyses will be performed using SAS version 9.4 (SAS Institute, Cary, NC).

**Power Estimates**: There will be 90 dyads randomized to each condition, with at least 63 per condition (30% dropout) expected at the 2-month assessment. PASS 16 was used to estimate power and effect size based on this sample size. Aim 1 hypothesizes that average caregiver burden will be lower in the FOCUS vs UC condition at 2 months. With alpha=.025, a two-sided test, and group n’s of 63, it is estimated that power

>.80 to detect a standardized difference between means of 0.56, which can be described as slightly greater than a medium effect size. Aim 1 also hypothesizes that average caregiver burden will be lower in the FOCUS vs HL condition at 2 months. Under the same conditions as above, but with alpha set at .05, it is estimated that power >.80 to detect a standardized difference between means of 0.51, a medium effect size. Power estimates for the hypotheses to be tested in Aim 2 (e.g., patient distress) parallel those for Aim 1. It is possible that fewer patients will agree to participate and the minimum effect sizes will be higher than those for Aim 1 (e.g., if group n’s=50, then effect sizes increase to 0.62 [UC] and 0.57 [HL]).

**Specific Aim 1**: Aim 1 is to evaluate the efficacy of FOCUS when compared to UC and HL on caregiver burden. H1a and H1b: Caregivers in FOCUS will report lower levels of burden 2 months post-treatment than caregivers in UC (H1a) and HL (H1b). The primary predictors of the GEE model are condition (e.g., FOCUS vs UC), time (end of treatment [8 weeks] vs 2 months), and their interaction. The GEE will include as a covariate any baseline measure that differs by group (p<.05) as a potential confound (e.g., age, relationship to patient, baseline burden). Other covariates will be predictors of missing follow-up surveys and/or self-reported burden at 8 weeks or 2 months (p<.05). These covariates will increase the viability of the Missing at Random assumption and improve parameter estimates within a full information maximum likelihood model. As described above, H1a will be assessed at alpha=.025 and H1b at .05. Each hypothesis will be tested using a planned contrast of condition at 2 months assessing the prediction that FOCUS will have a lower mean burden than the comparison condition (UC or HL). A significant main effect for condition would be another indicator of group differences (burden averaged over the 2 assessments).

Additional analyses will be performed to assess the effect of FOCUS on burden at the 6 month follow- up. A new GEE model will incorporate the three assessments of burden (8 weeks, 2 months, and 6 months) using appropriate covariates. The primary test will be a planned contrast of condition at 6 months. A separate model is justified by 1) the expected increase in missing surveys at 6 months and 2) the expected addition of covariates that predict missing surveys and/or burden at 6 months. This test at the 6-month follow-up will also be conducted for aim 2 outcomes of patient distress and healthcare utilization.

**Specific Aim 2**: Aim 2 is to evaluate the impact of FOCUS on patient health and patient healthcare utilization. H2a and H2b: Patients of caregivers in FOCUS will report lower levels of distress 2 months post- treatment than patients of caregivers in UC (H2a) or HL (H2b). Exploratory: Determine the impact of FOCUS on patient healthcare utilization in the first 2 months and from 3 to 6 months post-treatment (hospital readmissions, length of readmissions, unexpected patient clinic visits). The analysis for this hypothesis parallels that of Aim 1. The main differences are the outcome measure and the sample. If preliminary analyses show that distress exhibits sufficient characteristics to be treated as a continuous variable, then the identity link and linear regression will be used within the GEE. If not, an appropriate link function and regression approach will be applied. The sample of patients has potential to have more missing surveys, to have different predictors of missing surveys, and to have unique predictors of distress. Therefore, these GEE models are likely to have different sets of covariates (e.g., number of serious transplant complications; acute GVHD; relapse).

Similar GEE models will be used to explore group differences in patient healthcare utilization through 2 months and from 3 to 6 months. As noted above, model covariates may differ. The main difference in these models will be driven by the distribution characteristics of the healthcare utilization measures. For those measures that cannot be considered continuous, the link function and regression type within the GEE will be changed to an option that best matches the outcome distribution (e.g., link=binary, regression=logistic for whether or not there were unexpected patient clinic visits).

**Specific Aim 3**: Aim 3 is to evaluate putative mechanisms and moderators of FOCUS. Prospective mechanisms of lower perceived burden are higher mindfulness and self-efficacy, and lower stress and negative affect. The measure of these variables at 2 months (6 months for cortisol) post-treatment will be evaluated using the same approach described for the analyses in Aim 1.

These variables will also be assessed within the daily diary component of the study, which allows for 2 additional opportunities to assess mechanisms. First, the repeated, daily measures will be assessed using GEE for condition comparison with an emphasis on the main effect of condition (averaged over the multiple daily measures) and the condition x time interaction (diverging trajectories with the group differences increasing over time). Second, the repeated, daily measures of an active mechanism variable and the measures of burden at 8 weeks and 2 months will be entered into a structural equation model designed to evaluate whether or not changes in an active mechanism variable precede changes in burden. Mplus version

8.4 will be used for these models.149

Potential moderators (e.g., gender, age, relationship to patient, income, proximity to cancer center [defined as the mileage of home residence from Moffitt], baseline caregiver distress) of FOCUS on caregiver burden will be evaluated by adding to the GEE model for Aim 1 the moderator (e.g., gender) and its interaction with condition. A significant interaction will be further explored by testing differences in burden for each condition within appropriate subsets of the moderator (e.g., male and female).

**Data management**. Study data will be managed through REDCap (Research Electronic Data Capture), a data management software system supported and provided free by Moffitt. REDCap allows creation of customized, secure data management systems including web-based data entry forms, reporting tools, and a full array of security features including user and group-based privileges with a full audit trail of data manipulation and export procedures. Nationally, REDCap software is developed, enhanced, and supported through a multi- institutional consortium led by Vanderbilt University. The Project Manager, along with the Research Coordinator, will oversee creation of the database, questionnaires, and an automated messaging system.

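### The primary GEE is credited with validity under missing-at-random dropout and with a full-likelihood basis, neither of which it has as specified; the resulting bias is probably small but not guaranteed to be

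*Protocol*

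**What the plan says.** Protocol, Data Management and Statistical Considerations: the primary method for Aims 1 and 2 is "generalized estimating equations (GEE) with an identity link function, linear regression, and compound symmetry for the working correlation matrix". Among its listed advantages is that it will "help effectively manage missing data by study completers under the missing at random assumption (MAR"). Multiple imputation is not committed to; preliminary analyses will assess "whether or not multiple imputation for managing missing data would be beneficial". Weighting is not mentioned.

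Protocol, Specific Aim 1: the model terms are condition, "time (end of treatment [8 weeks] vs 2 months), and their interaction". Covariates come from two sources. The first: "The GEE will include as a covariate any baseline measure that differs by group (p<.05) as a potential confound". The second: "Other covariates will be predictors of missing follow-up surveys and/or self-reported burden at 8 weeks or 2 months (p<.05"). These are said to make the missing-at-random (MAR) assumption more tenable and to "improve parameter estimates within a full information maximum likelihood model".

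For the later follow-up, the same section says: "A new GEE model will incorporate the three assessments of burden (8 weeks, 2 months, and 6 months) using appropriate covariates".

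Power Estimates plans for 30% dropout, from 90 to 63 per arm, at the primary 2-month assessment.

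**The concern.** The two statements give the primary estimator properties that belong to a different estimator. GEE solves moment equations for the means and uses a working correlation only as a weight. A full information maximum likelihood model specifies a joint distribution, and that is what makes it valid under MAR without modelling the dropout. Unweighted GEE carries a general guarantee only when missingness is completely random or depends on covariates in the mean model.

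The planned covariates narrow this gap but cannot close it. A natural driver of dropout at 2 months is burden reported at end of treatment. In this model that value is a response, so it cannot also be a covariate. Protection against dropout that depends on it rests on the compound-symmetry working correlation being close to the truth.

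At stake is the 2-month contrast for H1a and H1b, and the 6-month contrast, where the protocol itself expects more missing surveys. Dropout that differs by arm is plausible, since FOCUS and Healthy Living have six sessions and Usual Care has none. A reader who trusts the two statements would see no reason for a safeguard.

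**Working it through.** **1. The plan's own figures.** 90 × 0.70 = 63 per arm; 270 × 0.70 = 189. Power by normal approximation is Φ(d·√(n/2) − z), with √(63/2) = 5.612.
- FOCUS vs UC: 0.56 × 5.612 − 2.241 = 0.902, power 0.816 (0.808 by noncentral t).
- FOCUS vs HL: 0.51 × 5.612 − 1.960 = 0.902, power 0.817 (0.811 by noncentral t).

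Both stated figures (>.80) reproduce, and nothing below changes them.

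**2. What the specified GEE estimates.** Take two visits, identity link, separate means by arm and visit, and working correlation α. Solving the equations within an arm gives:

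2-month mean (GEE) = completers' 2-month mean + α × (mean end-of-treatment burden of all − that of completers).

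Normal-theory likelihood has the same form, with the regression slope β = ρ·s2/s1 in place of α. Here ρ is the within-person correlation, and s1 and s2 are the SDs at end of treatment and 2 months. If dropout depends on end-of-treatment burden, the bias of the arm contrast in 2-month SDs is

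(β − α) × D × s1/s2,

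where D is the between-arm difference in how far completers' end-of-treatment mean is shifted by dropout, in end-of-treatment SDs. The bias vanishes if D = 0 (dropout acts alike in both arms) or α = β. GEE's α differs from β in two ways. It is estimated from complete pairs, whose spread dropout has narrowed, and it assumes one common variance.

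**3. Assumptions (not in the documents).** ρ from 0.4 to 0.8; s2/s1 from 0.7 to 1.3, plus a rise from 0.7 to 1.0; 30% logistic dropout on end-of-treatment burden with log-odds slopes of 0, +1 or −1 per SD. For opposite slopes (+1/−1), α = 0 at ρ = 0.6 gave a simulated bias of −0.303. With α = 0 the formula reduces to ρ·D, so D = −0.303/0.6 = −0.505.

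**4. Two-visit model, opposite slopes.**

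| ρ | s1, s2 | α (simulated) | β | Formula | Simulated bias |
|---|---|---|---|---|---|
| 0.6 | 1, 1 | 0.558 | 0.600 | 0.042 × (−0.505) = −0.021 | −0.021 |
| 0.6 | 1, 1.3 | 0.564 | 0.780 | 0.216 × (−0.505)/1.3 = −0.084 | −0.083 |
| 0.6 | 1, 0.7 | 0.500 | 0.420 | −0.080 × (−0.505)/0.7 = +0.058 | +0.054 |
| 0.8 | 1, 1 | 0.752 | 0.800 | 0.048 × (−0.505) = −0.024 | −0.022 |
| 0.8 | 1, 1.3 | 0.762 | 1.040 | 0.278 × (−0.505)/1.3 = −0.108 | −0.111 |
| 0.6 | 0.7, 1 | 0.558 | 0.857 | 0.299 × (−0.505) × 0.7 = −0.106 | about −0.11 |
| 0.8 | 0.7, 1 | 0.752 | 1.143 | 0.391 × (−0.505) × 0.7 = −0.138 | about −0.13 to −0.14 |

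Other dropout patterns, with s2/s1 from 0.7 to 1.3:
- Same slope in both arms: bias within 0.002 SD.
- Slope in one arm only: 0.004 to 0.005 SD with equal SDs, 0.024 to 0.047 SD with unequal SDs.
- Gaussian maximum likelihood: within 0.003 SD in every scenario.

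**5. Three-visit 6-month model.** With equal SDs, adjacent-visit correlation of 0.6 to 0.7 that decays with distance, and dropout that differs by arm, the bias at 6 months is about 0.03 to 0.07 SD. One constant correlation cannot fit a decaying pattern, so bias arises here without any change in SD.

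**6. At trial size.** With 90 per arm, ρ = 0.6, equal SDs, opposite slopes and 300 replicates, GEE bias was about −0.02 SD with 6.7% rejections at nominal 5%. The Monte Carlo error is √(0.05 × 0.95/300) = 1.3 points, so this is not distinguishable from 5%.

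**7. What the covariates achieve.** When baseline burden instead drives dropout, with opposite slopes, the bias is −0.12 SD if baseline is left out and −0.01 SD if it is included.

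**The case against.** The strongest reply is that the label is wrong but the method is nearly right. With an identity link, two visits and compound symmetry, the mean equations have the Gaussian likelihood form. Large bias (0.10 to 0.41 SD with arm-differential dropout) appears only with an independence working correlation, which the protocol does not choose. This stands, and it is why the equal-SD bias is about 0.02 SD.

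The simulation is also harsh. All 30% leave after giving end-of-treatment data, and no covariates are used. With a baseline covariate, and dropout split 15% before (at random) and 15% after end of treatment, the bias was at most 0.005 SD with equal SDs, at most 0.02 SD for SDs of 0.9 to 1.0, and 0.055 SD for 0.7 to 1.0 with opposite slopes. The contrast's standard error is √(2/63) = 0.18 SD. The Project Overview expects little missing data at 2 months; if so, the bias shrinks further. All this lowers the size but does not make the two statements true.

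Three stronger readings are tempting but unsupported:
- A reader might infer that SDs must change sharply because the visits straddle the peri-transplant and post-Day-100 periods. In the primary model they do not. Baseline is not a repeated outcome. Consent at about Day −14 plus 8 weeks puts end of treatment near Day +42, and 2 months later is near Day +100. The last three sessions follow discharge, and the dyad is still expected to live near the center at 2 months.
- A reader might extend the bias to healthcare utilization through non-identity links. This was not simulated. Those outcomes are exploratory and mainly chart-based, so survey dropout does not carry over directly.
- A reader might treat the silence on weighting as the defect. A statistical analysis plan may settle that. The defect is what the protocol affirmatively says.

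**Conclusion.** The point holds as an error in the stated properties of the primary analysis. The maximum-likelihood description is wrong for GEE. The MAR claim is too broad unless weighting or imputation is added, and the protocol commits to neither. The Aim 3 structural equation models do not rescue the wording, because the sentence describes the covariates of the Aim 1 GEE.

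It would go too far to conclude that the primary 2-month contrast is materially biased. That needs dropout that differs by arm and SDs that differ between visits, and the documents give no figures on either. Within the assumed range the bias runs from zero to roughly 0.11 SD, about a fifth of the planned 0.51 to 0.56. It exceeds that (0.13 to 0.14 SD) only at the extreme corner of ρ = 0.8 with the SD rising from 0.7 to 1.0. Its direction cannot be known in advance. The 6-month contrast is somewhat more exposed, because decaying correlation alone is enough once dropout differs by arm. Confidence is high on the wording and moderate on the size. The correction is worth making before analysis but does not threaten the design.

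**What to change.** Either of two changes makes the text and the method agree.

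1. For continuous outcomes, fit the same fixed effects and planned contrasts at 2 and 6 months with a likelihood-based repeated-measures model with unstructured covariance. The MAR and maximum-likelihood statements then become true. Keep the compound-symmetry GEE as a sensitivity analysis.
2. Or keep GEE as primary, delete the maximum-likelihood wording, and limit the missing-data claim to missingness that depends on modelled covariates. Commit in advance to multiple imputation before GEE, with end-of-treatment burden in the imputation model, or to inverse-probability-weighted GEE, instead of deciding on imputation after inspecting the data.

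If GEE is kept for survey outcomes that are not continuous, such as patient distress should it need another link, apply imputation or weighting there too.

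The cost is a wording change and slightly more analysis work. Data, visits, contrasts, software and sample size stay the same. Option 1 relies on the modelled covariance, which the unstructured form and the GEE sensitivity analysis largely cover; option 2 relies on the imputation or dropout model.

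### The protocol names Holm but fixes alpha by comparison (.025 for UC, .05 for HL); followed literally, experiment-wise error is about 7%, not at most 5%

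*Protocol*

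**What the plan says.** In the Protocol, Data Management and Statistical Considerations, the method and its purpose are named: "The Holm method148 will be applied to control for experiment-wise error in the primary analyses". The same sentence goes on "with alpha set at .025 for tests of FOCUS vs UC and set at .05 for FOCUS vs HL".

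Specific Aim 1 repeats the assignment by hypothesis: "As described above, H1a will be assessed at alpha=.025 and H1b at .05". H1a is FOCUS vs UC and H1b is FOCUS vs HL. Each is tested by the condition contrast at the 2-month assessment.

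Power Estimates uses the same levels. For UC: "With alpha=.025, a two-sided test, and group n’s of 63, it is estimated that power" exceeds .80 at a standardized difference of 0.56. For HL: "Under the same conditions as above, but with alpha set at .05", power exceeds .80 at 0.51. For Aim 2, both the power estimates and the analysis are said to parallel Aim 1.

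Nowhere does the protocol say that the p-values are ordered, that .05 applies only to the larger one, or that testing H1b depends on rejecting H1a.

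**The concern.** Holm decides after the data are in which comparison faces .025. The protocol decides it in advance and gives the more lenient level to HL unconditionally. One sentence therefore contains two different decision rules, and only one of them has the error control that the sentence claims.

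The choice can decide what the trial reports on its primary outcome:

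| p(UC) | p(HL) | Holm | Levels as written |
|---|---|---|---|
| .04 | .03 | smaller p .03 > .025: rejects neither | rejects HL (.03 < .05), not UC |
| .04 | .01 | .01 ≤ .025, then .04 ≤ .05: rejects both | rejects HL only (.04 > .025 for UC) |

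The written levels claim too much in the first case and lose a valid claim in the second. If the ambiguity is still open when results by condition are known, the choice of reading could settle whether a hypothesis is declared supported.

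**Working it through.** **Inputs from the protocol.** 1:1:1 allocation; "There will be 90 dyads randomized to each condition, with at least 63 per condition (30% dropout) expected at the 2-month assessment", that is 90 × 0.70 = 63 per arm; two-sided tests; levels .025 (UC) and .05 (HL); standardized differences 0.56 (UC) and 0.51 (HL). The check uses pairwise two-sample comparisons of means, not the GEE model itself.

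**1. Reproduce the stated power.** Normal approximation: power = Φ(d√(n/2) − z), with √(63/2) = 5.612, z = 2.241 for .025 and z = 1.960 for .05.

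- UC: 0.56 × 5.612 − 2.241 = 0.902, power 0.816 (0.808 by noncentral t).
- HL: 0.51 × 5.612 − 1.960 = 0.902, power 0.817 (0.811 by noncentral t).

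The arithmetic is right for the levels used.

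**2. Experiment-wise error with both nulls true.** The two contrasts share the FOCUS arm. With equal arms their covariance is σ²/n and each variance is 2σ²/n, so the correlation is 0.5.

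- As written: 1 − P(|Z_UC| < 2.241 and |Z_HL| < 1.960) = 0.069 at correlation 0.5. A simulation of 400,000 trials with three arms of 63 gives 0.0687.
- As written, if independent: 1 − 0.975 × 0.95 = 0.07375. Upper bound: .025 + .05 = .075.
- Holm: 1 − P(both |Z| < 2.241) = 0.0465 (simulation 0.046).

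If only one null is true, the written rule tests it at .025 or .05, so the excess over 5% arises only when both are true.

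**3. Power under each rule (same simulation, n = 63 per arm).**

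| True effects (UC, HL) | UC as written | UC Holm | HL as written | HL Holm |
|---|---|---|---|---|
| 0.56, 0.51 | 0.809 | 0.846 | 0.811 | 0.786 |
| 0.51, 0.51 | 0.723 | 0.777 | 0.811 | 0.776 |
| 0, 0.51 | – | – | 0.810 | 0.725 |

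**4. How often the rules disagree at the planned effects.** Holm can only add UC rejections and only remove HL rejections relative to the written levels, and the two events cannot occur together. So the rate is (0.8458 − 0.8087) + (0.8107 − 0.7862) = 0.0371 + 0.0245 = 0.062, about 6%.

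**5. Detectable difference at .025.** Under Holm, HL is always rejected when its p-value is at most .025. The difference with 80% power at that level is 0.555 for n = 63 and 0.625 for n = 50 (noncentral t), whatever happens with UC. The protocol gives 0.51 and 0.57 for HL.

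**The case against.** The best defence is that Holm is the operative instruction, with its source cited, and that the named levels are shorthand for an expected order: UC gives the smaller p-value, then HL is tested at .05. If Holm is run as named, or HL is tested only after UC is rejected at .025, error stays within 5%. This is a fair reading of intent, so the 7% cannot be presented as what will certainly happen. But the gate is not written, and the levels appear three times without a condition. On the gated reading, HL power at the planned effects is 0.70, so the stated HL power fails there too.

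Other points that stand in part:

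- **Direction.** H1a and H1b are directional. Counting only rejections in favour of FOCUS, the figures are 3.5% against a nominal 2.5%. The relative excess is much the same.
- **Joint claim.** If success meant beating both comparators, the written levels would not inflate error with both nulls true (0.6%). But H1a and H1b are set out as separate hypotheses, each with its own level.
- **Size of the power loss.** A reader might infer that HL power is really 72%. That figure needs FOCUS to have no effect against UC, which sits badly with a design where HL is not expected to affect burden and UC receives the same booklet. At the planned effects the loss is about 2 points.
- **Main effect.** Specific Aim 1 adds: "A significant main effect for condition would be another indicator of group differences". A reader might infer a further unadjusted route to success. The text does not support this. It fixes the 2-month contrast as the test of each hypothesis and gives the main effect no level, so no inflated error rate should be attached to it.

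**Conclusion.** The protocol contradicts itself on its primary decision rule. Levels fixed by comparison, without ordering or gate, are not Holm. Followed literally, they give about 6.9% two-sided experiment-wise error with both nulls true (7.4% if independent), against about 4.6% for Holm and an intended maximum of 5%. This rests on equal arms of 63, a correlation of 0.5 from the shared arm, and the literal reading. The protocol does not establish that the analysts would follow that reading, only that it is what the text says.

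The effect on power is modest. Under Holm at the planned effects, UC has about 85% and HL about 79%. The HL statement is therefore slightly overstated, falling to 72–73% only if FOCUS does not differ from UC. Because Aim 2 follows Aim 1, H2a and H2b inherit the same contradiction. No separate statistical analysis plan was available. One could settle the matter, but the protocol's statement would still need correcting.

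**What to change.** Replace the fixed levels in Data Management and Statistical Considerations and in Specific Aim 1 with the Holm rule itself: the smaller of the two p-values is tested at .025, and only if it is rejected is the larger tested at .05. Alternatively, prespecify another valid scheme, such as a fixed sequence with the gate written out. State that the same rule applies to H2a and H2b.

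Restate power under the rule chosen. For Holm with 63 per arm and effects of 0.56 (UC) and 0.51 (HL): about 85% and 79%. A statement for HL that does not depend on the UC result is a difference of about 0.56 for 80% power (about 0.625 with 50 per arm). Avoid describing 0.51 as the detectable difference given that UC is rejected first: with a shared arm, HL power given UC rejection at .025 is about 0.7004 / 0.8087 = 87%, not 81%.

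It is also worth a sentence saying that the time-averaged main effect is supportive only.

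The cost is wording and a slightly less favourable HL power statement. Sample size, endpoints, model and data collection are untouched. The change should be made before results by condition are seen.

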A subsample of patients will be asked to complete a telephone interview (approximately 30-45 minutes in length) in order to obtain feedback about the possibility of having patients engage in a stress management intervention in a future study. Approximately 30 patients whose caregivers were randomized to either the HL or FOCUS interventions will be asked to participate in the phone interviews at approximately the 2-4 month post EOT follow up period. Every other patient enrolled with a caregiver in one of those two conditions will be asked to participate in an individual phone interview. The number of patients asked to participate will be approximately 15 per caregiver’s condition (HL or FOCUS) or until saturation of feedback (i.e., no new information is offered by participants). Approximately 20 open ended questions will include queries about the patient’s emotional and physical experience around the transplant process, including the pre-hospitalization, hospitalization for transplant, and post-hospitalization periods. Specifically, stress, coping, stress management, and awareness of caregiver’s stress management program will be queried. Patients will also be asked for their thoughts about offering stress management to patients and what types of support would have been useful. Interviews will be recorded, transcribed, and coded for themes.

**Randomization.** Participants (caregiver/patient dyads) will be randomized at enrollment, to one of the three treatments using balanced-permuted blocks of size six toward assigning 90 dyads to each condition. Caregivers will be stratified by gender prior to randomization as research indicates male and female cancer caregivers differ on distress and coping styles.114

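### Primary-model covariates are chosen by p<.05 tests on the trial data, so the primary model is not fixed in advance and neither baseline burden nor gender has a guaranteed place in it

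*Protocol*

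**What the plan says.** Specific Aim 1 lists the fixed terms: "The primary predictors of the GEE model are condition (e.g., FOCUS vs UC), time (end of treatment [8 weeks] vs 2 months), and their interaction". Only the 8-week and 2-month scores are therefore in the outcome vector; baseline burden is not part of it.

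Other covariates enter by one of two routes, both tested at p<.05:

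- **Imbalance test.** "The GEE will include as a covariate any baseline measure that differs by group (p<.05) as a potential confound". Baseline burden appears only among the examples: "e.g., age, relationship to patient, baseline burden". Data Management and Statistical Considerations states the same rule for hypothesis tests in general: "Paired comparisons will be used to identify group differences, despite randomization, in demographics, clinical, and psycho-social variables".
- **Missingness and outcome screen.** "Other covariates will be predictors of missing follow-up surveys and/or self-reported burden at 8 weeks or 2 months (p<.05". The Aim 2 text speaks separately of what predicts missing surveys and what predicts distress, which supports reading this sentence as two screens, one of them on the outcome.

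The Randomization paragraph says: "Caregivers will be stratified by gender prior to randomization". In the analysis, gender is named only under Specific Aim 3, where moderators are tested by "adding to the GEE model for Aim 1 the moderator (e.g., gender) and its interaction with condition". No section commits baseline burden or gender to the primary model.

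**The concern.** This is a stated rule, not a detail left open for an SAP, and it has three weaknesses.

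1. Under randomisation every baseline difference between arms is due to chance. A significance test on such differences picks covariates by luck and says nothing about prognostic value.
2. Gender is balanced by design, so the imbalance test will essentially never select it. Yet the protocol's reason for stratifying is that male and female caregivers differ in distress and coping, which treats gender as prognostic.
3. The second route tests candidates against the primary outcome. The primary model then depends on the data and cannot be written down before follow-up data are seen.

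At stake are the pre-specification of H1a and H1b and some of their precision.

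**Working it through.** **Inputs from the protocol (Power Estimates, Randomization, Table 4).** 90 per arm; 30% dropout, so 90 × 0.7 = 63 per arm; two-sided alpha .025 with d = 0.56 (UC) and .05 with d = 0.51 (HL); blocks of six within gender. The caregiver demographics paragraph names nine variables and Table 4 lists about 19 other baseline caregiver measures, so 9 + 19 = 28 candidates; 30 is assumed below. The correlation r between baseline and follow-up burden is not given and is assumed.

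**Stated power.** Two-sample noncentral t, df = 124, noncentrality d√(63/2):
- UC: 0.56 × 5.612 = 3.14, power 0.808.
- HL: 0.51 × 5.612 = 2.86, power 0.811.

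Both agree with the stated >.80, and both are unadjusted calculations.

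**Imbalance test.** Each candidate passes with probability 0.05 per comparison (simulated 4.7 to 5.2%), so 30 × 0.05 = 1.5 chance covariates are expected per comparison. For gender, an unfinished block of six leaves two arms at most 2 apart within a stratum. With 90 per arm and half of caregivers female (assumed), p<.05 needs a gap of about 1.96 × √(2 × 0.25/90) = 0.146, or 13 caregivers. In 4,000 simulated stratified comparisons (70% or 50% female) gender never reached p<.05.

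**Outcome screen and baseline burden.** Probability of admission ≈ 1 − Φ(1.96 − atanh(r)√(N − 3)), for N = 126 (two arms) and N = 189 (three arms):

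| r (assumed) | N = 126 | N = 189 |
|---|---|---|
| 0.1 | 0.20 | 0.28 |
| 0.2 | 0.61 | 0.79 |
| 0.3 | 0.93 | 0.99 |
| 0.5 | 1.00 | 1.00 |

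Simulating both routes with a true d = 0.56 in two arms gave 0.91 to 0.92 at r = 0.3 and 1.00 at r = 0.5.

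**Fixed adjustment for baseline burden.** Replace d by d/√(1 − r²). For UC at r = 0.3, 0.56/0.954 = 0.587 and power is 0.846; at r = 0.5, 0.56/0.866 = 0.647 and power is 0.912.

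**The rule with one candidate (baseline burden only).** At r = 0.5 and d = 0.56, power is 0.911 under both routes together and 0.911 under fixed adjustment. The imbalance test alone would give 0.815.

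**The rule with 30 candidates.** Baseline burden plus 29 unrelated variables, 63 per arm, one time point, alpha .025, d = 0.56. Expected surplus covariates when there is no treatment effect: 29 × (1 − 0.95²) = 2.8.

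| r (assumed) | Power under the rule | Power, baseline burden fixed | Loss |
|---|---|---|---|
| 0.3 | 0.805 | 0.843 | 3.8 points |
| 0.5 | 0.886 | 0.916 | 3.0 points |

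A separate run at r = 0.5 gave 0.87 against 0.91. At r = 0.3 the rule does no better than the unadjusted 0.808: the surplus covariates, chosen because they line up with arm or outcome, compete with the condition term and use up the gain from baseline burden.

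**Type I error at nominal .025.** One candidate, both routes: 0.024 to 0.025. Thirty candidates: 0.024 to 0.029, Monte Carlo standard error about 0.002.

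**The case against.** The strongest reply is that the second route does the job. It selects on prognosis, and at r = 0.3 or above it brings baseline burden in nearly every time; where it fails (r of 0.1 to 0.2), adjustment is worth little. This stands. A reader might infer that the plan forgoes a rise in power from 81% to 91% at r = 0.5, but that compares fixed adjustment with an unadjusted model that the protocol does not plan.

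Three other stronger readings also fail:

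- **That the selection biases the test.** The simulations show no clear type I inflation.
- **That covariates are chosen on unblinded outcomes.** Candidates can be screened against burden or missingness in pooled data without arm codes, and no section says otherwise. Only the imbalance test needs the arms. The supportable description is data-dependent.
- **That leaving gender out invalidates the analysis.** Omitting a balanced stratification factor tends to make the test slightly conservative. If gender does predict burden, the second route can admit it. No loss was quantified for gender.

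An SAP could also fix the candidate list and the mechanics of screening. That would limit analyst discretion, but while the protocol's p<.05 rule stands the model would still be decided by the data.

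**Conclusion.** The point holds as one of pre-specification and modest efficiency, not of validity. Neither baseline burden nor gender is guaranteed a place in the primary model. For baseline burden, omission is unlikely unless r is well below 0.3. For gender the gap is firmer, since the imbalance route is closed by design and the other depends on what the data show.

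The estimated cost is 3 to 4 points of power for H1a. It rests on 30 assumed candidates of which only baseline burden is prognostic, independent normal covariates, one time point and the assumed r. Other prognostic or correlated candidates would change the figure. Wider analyst discretion was not simulated.

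**What to change.** In Specific Aim 1, state that the primary GEE for H1a and H1b includes condition, time, condition-by-time, baseline ZBI and gender (the stratification factor) as fixed covariates, whatever their p-values.

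Delete the baseline-difference test and the p<.05 outcome screen as routes into the primary model, and amend the matching general sentence in Data Management and Statistical Considerations. To keep the support for the missing-at-random assumption, retain missingness predictors as a short list of baseline variables named in advance, or use them as imputation auxiliaries or in a sensitivity analysis.

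The cost is wording only: gender is known at randomisation and the ZBI is already scheduled at baseline in Table 4.
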